### Statistical analysis

#### Sample size

Because laparoscopic liver surgery focuses on accelerated recovery, time to functional recovery is used as the primary outcome parameter. Owing to the lack of hard evidence about the reduction in time to functional recovery after liver surgery, we have chosen to use the parameter that most accurately approaches our primary endpoint for our power calculation (LOS). Based on a retrospective analysis of 31 patients in both ERAS and non-ERAS settings, who have undergone LLS from 1990 to the present time, the mean ± SD post-operative hospital stay for a LLS in the Maastricht University Medical Center is 6 ± 2.73. It therefore seems that that in patients undergoing laparoscopic LLS, time to functional recovery is reduced in comparison to patients undergoing the open procedure. We are aiming for a reduction in time to functional recovery of 2 days. A sample size of 2 × 40 patients in the randomisation arms will be sufficient to show a 2-day reduction with a power of 90% and a level of significance at α = 0.05 (two-tailed, given a within-arm SD of 2.73 with effect size *d* = 0.73). Assuming an expected withdrawal rate of ≤ 10% during the trial, the participation of at least 10 centres, and the required addition of one randomised patient per arm for every additional participating centre (C) to compensate for the loss of degrees of freedom incurred in the data analysis, which takes centre and treatment × centre effects into account, a total sample size of 110 (n = 2 × 55) will be required.

For all secondary outcome measures, the power will be 75% after correction for multiple testing with two-tailed α = 0.01, assuming the same effect size (*d* = 0.73) as for the primary outcome. An interim analysis of the primary outcome, using Snapinn’s method, will be performed after inclusion of 50% of the sample to avoid unnecessary inclusion of too many patients in this ORANGE II trial [56].

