### Primary & secondary endpoints

The primary endpoint of the ORANGE II trial is time to functional recovery. A patient is fully functionally recovered when all of the following five criteria are satisfied: 1) adequate pain control with oral analgesia; 2) restoration of mobility to an independent level; 3) absence of intravenous fluid administration; 4) ability to eat solid foods; and normal or decreasing serum bilirubin level and international normalised ratio.

It is medically justified to discharge patients when the criteria for full functional recovery are met and if the patient is willing to go home. Secondary endpoints include postoperative LOS in hospital, percentage of readmissions, total morbidity (both general and procedure related), composite endpoint of liver-surgery-specific morbidity, QOL, body image and cosmesis, reasons for delay of discharge after functional recovery, hospital and societal costs over 1 year, and long-term incidence of incisional hernias.

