#### Univariate analysis

The primary outcome measure of time to functional recovery will be measured in days, and will be analysed with fixed-effect regression that will take centre and treatment × centre interaction into account as fixed effects. If the actual number of centers and the sample size per centre allow random effects analysis, this will also be performed and this analysis will have the same power as the planned fixed effects analysis if the design effect does not exceed 1.2. With a sample size of 10 patients per centre, the design effect is 1.2 if the intraclass correlation (ICC) is 0.02, where the ICC is based on treatment × centre interaction [57].

All secondary outcomes as measured at discharge will be analysed by fixed-effect regression using linear regression for quantitative outcomes and logistic regression for binary outcomes, and including the baseline measure as a covariate to improve power and precision. In addition to *P*-values, confidence intervals for all effects will be reported. Morbidity will be classified as described by Dindo *et al*., but will be presented as raw data only because the required sample size for intervention effects on morbidity is much larger than the calculated sample size for this trial [58].

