## Discussion

Several authors have indicated that laparoscopic liver resection has many benefits over conventional open liver resection. However, this has never been proven in an RCT, and what the primary endpoint should be for an RCT comparing open and laparoscopic liver resection is a subject to debate. Using either liver surgery-related mortality or liver surgery-specific morbidity as an endpoint is not feasible, because patient accrual would take many years and be a logistically major global effort [58]. LOS in hospital, time to recovery, long-term incisional hernias, body image, and costs are potential candidates because improvements in these are some of the possible benefits. Laparoscopic liver resection is appealing for many surgeons and patients, but the learning curve for the surgeon is thought to be long and costly for hospital budgets. However, operating times in laparoscopic LLS tend to be shorter, and may compensate for expenses in technology and consumables [31,59]. Moreover, the existing trials in liver surgery have not evaluated time to recovery or LOS in hospital after laparoscopic liver resection within an enhanced recovery programme. The more rapid recovery reported after enhanced recovery programmes may be further accelerated as a consequence of small incisions in laparoscopic surgery. In addition, learning curves for laparoscopic left lateral resection or anterior segments seem to be reasonably short for liver surgeons with advanced laparoscopic experience [60]. The question remains whether an RCT is necessary to prove that laparoscopy should be accepted as the preferred method to perform liver resection. In the Louisville consensus meeting on laparoscopic liver surgery, it was stated that laparoscopic LLS should be standard practice in experienced hands [61]. However, this may have been a subjective vision of a subset of opinion leaders, because long experience with both open and laparoscopic liver surgery was the main characteristic of those attending the meeting. Undoubtedly, the dissemination phase of laparoscopic liver surgery has started, and it is to be expected that many surgeons will adopt this technique in the future. A multinational multicentre prospective registry, a well-organised multicentre RCT, training programmes, and quality control measures are of great importance during this adoption period [33].

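### The 75% power stated for all secondary outcomes holds only for the quantitative ones; it conflicts with the protocol's own statement on morbidity and is not met for readmission or incisional hernia at most plausible rates

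*Protocol article*

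**What the plan says.** The Sample size section bases the trial on 40 patients per arm for a 2-day difference with a standard deviation of 2.73. It raises this to 55 per arm for withdrawal and centre effects. It then states: "For all secondary outcome measures, the power will be 75% after correction for multiple testing", with a two-tailed alpha of 0.01, and adds the condition "assuming the same effect size (*d* = 0.73) as for the primary outcome".

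The Primary & secondary endpoints section shows which outcomes this covers: "Secondary endpoints include postoperative LOS in hospital, percentage of readmissions, total morbidity", followed by the liver-specific composite, quality of life, body image and cosmesis, reasons for delayed discharge, costs and incisional hernia. The section on the composite defines it as dichotomous. The Univariate analysis section assigns logistic regression to binary outcomes.

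Two other places say the reverse for morbidity. The Univariate analysis section gives it as raw data only because "the required sample size for intervention effects on morbidity is much larger than the calculated sample size for this trial". The Discussion says: "Using either liver surgery-related mortality or liver surgery-specific morbidity as an endpoint is not feasible".

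The Descriptive statistics section says that incisional hernia will be analysed as well as reported. Readmission is to be given as a percentage, and nothing restricts it to description.

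**The concern.** One sentence gives every secondary outcome 75% power. Another says that the trial is far too small for one of them. Both cannot stand.

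The effect size behind the 75% is a standardised mean difference taken from length of stay. It has no direct meaning for an event rate, and at low rates no reduction can be that large.

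What is at stake is how null results will be read. Hernia and readmission matter to the case for laparoscopy. A non-significant result on either would sit beside a published claim of 75% power and could be taken as evidence of no difference, when the comparison had little chance of showing one.

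**Working it through.** **Inputs from the protocol article**
- d = 2/2.73 = 0.73, 40 per arm, and two-sided alpha 0.01 for secondary outcomes (Sample size).
- 55 per arm randomised with up to 10% withdrawal: 55 × 0.9 = 49.5, taken as 49 evaluable per arm (Sample size).
- Hernia rates: up to 20% at 10 years after open surgery; 6.3%, 4.7%, 5.4% and 21.7% for four incision types (Incidence of incisional hernias). The trial scans at about 1 year.

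**Assumptions:** all laparoscopic-arm rates, all readmission rates, and the 10% control rate. The article gives none of these for this trial, so a range is shown.

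**Step 1: reproduce the 75%.** Power ≈ Φ(d·√(n/2) − 2.576). With n = 40, 0.73 × √20 = 3.265, and Φ(3.265 − 2.576) = Φ(0.689) = 75.5%. The noncentral t gives 73.2%. The stated figure is therefore that of a two-sample comparison of means with 40 per arm.

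**Step 2: can d = 0.73 be carried to a binary outcome?** The protocol does not say how, so two common translations are tried.
- *Arcsine scale:* h = 2·asin√p1 − 2·asin√p2. With zero events in the other arm, the largest possible h is 2·asin√p1. Setting this to 0.73 gives p1 = sin²(0.365) = 12.7%. Below that control rate the effect cannot be reached. At 10% the ceiling is 0.64; at 6.3%, 5.4% and 4.7% it is 0.51, 0.47 and 0.44.
- *Logit scale:* odds ratio = exp(0.73·π/√3) = 3.76. From 20% this gives 6.2%, with power (normal approximation, alpha 0.01) of 28% at 49 per arm. From 10% it gives 2.9%, with power of 13%.

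**Step 3: power for pairs of rates.** Power = Σ Σ Bin(i; n, p1)·Bin(j; n, p2) over all outcomes (i, j) with p ≤ 0.01. The lower figure in each range is for Fisher's exact test and the upper for the uncorrected chi-square. Alpha is 0.01 two-sided.

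| Open vs laparoscopic | 49 per arm | 55 per arm (no loss) |
|---|---|---|
| 10% vs 5% | 1-3% | 2-4% |
| 20% vs 10% | 7-11% | 8-13% |
| 20% vs 5% | 27-36% | 33-43% |
| 21.7% vs 5% | 35-45% | 42-53% |
| 20% vs 1% | 66-77% | 77-85% |

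Hand check for 20% vs 10% at 49 per arm, by the normal approximation:
- null standard error = √(2 × 0.15 × 0.85/49) = 0.0721
- alternative standard error = √((0.16 + 0.09)/49) = 0.0714
- power = Φ((0.10 − 2.576 × 0.0721)/0.0714) = Φ(−1.20) = 11.5%, in line with the table.

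**Step 4: sample size for 75% power** (normal approximation, alpha 0.01): 102 per arm for 20% vs 5%, 269 for 20% vs 10%, and 586 for 10% vs 5%.

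**Basis.** The 75% was computed at 40 per arm. Using 49 or 55 for the binary outcomes favours the plan: at 49 per arm a quantitative outcome with d = 0.73 would have 84-85%, before any cost for centre terms. The shortfall is therefore not produced by a smaller n.

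**The case against.** The sentence is conditional on d = 0.73, and under that condition 75% is right. This stands. A reader might infer an arithmetic mistake, and there is none; the fault lies in applying the figure to every secondary outcome. The condition does not rescue that, because the assumed effect is out of reach at three of the four incision-specific hernia rates that the article cites.

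Morbidity is already limited to raw data, and the Descriptive statistics section can be read as placing the composite under the same limit. This also largely stands. A misread null result on morbidity is mostly forestalled, so the practical risk falls on readmission and hernia, and on the composite only if it is tested. The two statements about morbidity still contradict each other.

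The laparoscopic and readmission rates are assumed. This is true, and it is why a range is given. It also rules out the stronger reading that real power is a few percent throughout: it runs from about 1% to 45% over most of the pairs shown, and higher where events nearly disappear.

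A reader might also infer that alpha 0.01 is a Bonferroni share for five tests and too lenient for nine listed endpoints. The article names neither the method nor the test family, several listed items are descriptive, and an analysis plan not shown may define the family. Nor does a possible early stop at the interim analysis count against the sentence, which describes the planned sample.

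**Conclusion.** The point holds in limited form. The stated 75% is correct for quantitative secondary outcomes and should not be claimed for all of them.

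The contradiction with the statement on morbidity rests on the text alone and needs no assumption. The size of the shortfall for binary outcomes depends on the assumed rates: with 49 evaluable per arm, from about 1-3% (10% vs 5%) to 35-45% (21.7% vs 5%). Power comes near 75% only if an event rate of about 20% falls almost to zero. The cited 20% for hernia is a 10-year maximum, so a 1-year scan may well find less.

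The sample size, the primary analysis and its 90% power are unaffected.

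**What to change.** In the Sample size section:
- Limit the 75% statement to quantitative secondary outcomes at full enrolment.
- Add that readmission, incisional hernia and the liver-specific composite have low power, with figures over a stated range of assumed rates such as the table above.

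In the Univariate analysis section:
- Say that these binary outcomes are reported as estimates with confidence intervals, and that a non-significant result is not evidence of no difference.
- Say whether the composite falls under the raw-data-only rule for morbidity, so that the sections agree.

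The cost is wording only, with no change to the design, the sample size or the primary analysis. The downside is a less favourable stated power for the binary secondary endpoints.

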#### Descriptive statistics

The primary outcome parameter of time to functional recovery and the secondary parameter of LOS in hospital will be given in days, with a median and range. Morbidity will be classified according to the classification described by Dindo *et al*. and defined as a dichotomous composite endpoint, while readmission will be given as a percentage. Scores for quality of life, body image and cosmesis will be given as mean and standard deviation per time point per treatment arm. Hospital costs will be given as median and range. Long-term incidence of incisional hernia will be reported and analysed.

#### Univariate analysis

The primary outcome measure of time to functional recovery will be measured in days, and will be analysed with fixed-effect regression that will take centre and treatment × centre interaction into account as fixed effects. If the actual number of centers and the sample size per centre allow random effects analysis, this will also be performed and this analysis will have the same power as the planned fixed effects analysis if the design effect does not exceed 1.2. With a sample size of 10 patients per centre, the design effect is 1.2 if the intraclass correlation (ICC) is 0.02, where the ICC is based on treatment × centre interaction [57].

All secondary outcomes as measured at discharge will be analysed by fixed-effect regression using linear regression for quantitative outcomes and logistic regression for binary outcomes, and including the baseline measure as a covariate to improve power and precision. In addition to *P*-values, confidence intervals for all effects will be reported. Morbidity will be classified as described by Dindo *et al*., but will be presented as raw data only because the required sample size for intervention effects on morbidity is much larger than the calculated sample size for this trial [58].

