The Enhanced Recovery After Surgery (ERAS) programme has been introduced to improve postoperative care. This multimodal programme, derived from Kehlet’s pioneer work in the 1990s for multimodal surgical care, involves optimisation of several aspects of the perioperative management of patients undergoing major abdominal surgery. In patients undergoing segmental colectomy, the ERAS programme enabled earlier recovery and consequently shorter LOS [22-25]. Furthermore, a reduction of post-operative morbidity in patients undergoing intestinal resection was reported [26-29]. These results stimulated liver surgeons of the ERAS® group (Maastricht, Edinburgh and Tromsö) to adapt the ERAS programme to patients undergoing open liver resection. Van Dam *et al*. [30] found a significantly reduced LOS after open liver resection when patients were managed within a multimodal ERAS programme. Besides a reduction in median total LOS from 8 to 6 days (25%), the data also suggested that a further reduction in stay could be possible as there was a delay between the recovery and actual discharge of the patients [30]. Moreover, Stoot *et al*. found retrospectively that there was a further reduction in LOS from 7 days to 5 days when patients were operated laparoscopically and managed within an ERAS programme [31]. In that study there was also a delay between recovery and actual discharge of the patients. Previously, Maessen *et al*. reported a median delay to discharge of 2 days after patients had functionally recovered after colonic surgery managed within an ERAS programme [32]. This delay is often linked to patient age, hospital logistics, and absence of social and/or homecare support.

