#### Morbidity

The preoperative morbidity status of patients will be measured using the American Society of Anesthesiologists (ASA) scale. The Portsmouth modification of the Physiological and Operative Severity Score for the Enumeration of Mortality and Morbidity (P-POSSUM) will be used to evaluate the risk of perioperative morbidity and mortality. Post-operative morbidity is rationally predictable, with hemorrhagic complications occurring predominantly during surgery or in the early postoperative phase, and biliary complications, intra-abdominal abscess, or liver failure in the later postoperative phase. Wound infection and sepsis will be additional complications that require monitoring. Morbidity will be classified and analysed according to the validated classification for postoperative morbidity as described by Dindo *et al*[37].

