#### Mobility

To assess the difference between the preoperative and postoperative mobility level, the ERAS Mobility Scale (EMS) has been developed from the Groningen Activity Restriction Scale [55]. The EMS assesses 10 basic actions to compare the level of mobility before and after surgical intervention. When the patient is able to perform 8 of the 10 items, they are independently mobile. Patients will be assessed whether they are able or not to independently perform these basic actions fully. Daily the assessment will be repeated and compared with the preoperative baseline score until mobility at an independent or preoperative level is achieved.

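### The primary model names no patient-level baseline covariate; pre-specifying age, ASA grade and preoperative mobility would modestly improve precision

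*Protocol article*

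**What the plan says.** The protocol article, Univariate analysis, states that the primary outcome "will be analysed with fixed-effect regression that will take centre and treatment × centre interaction into account as fixed effects". No other term is named. Under Sample size, the step from 40 to 55 per arm allows for withdrawals and for the degrees of freedom used by these centre terms, and for nothing else.

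The next paragraph of Univariate analysis turns to other endpoints: "All secondary outcomes as measured at discharge will be analysed by fixed-effect regression", "including the baseline measure as a covariate to improve power and precision".

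Three patient characteristics are known before the operation:
- Age, which is an eligibility criterion (18 to 80 years).
- ASA grade: "The preoperative morbidity status of patients will be measured using the American Society of Anesthesiologists (ASA) scale". Grades I to III are eligible.
- The EMS score. Under Mobility, the postoperative score is "compared with the preoperative baseline score until mobility at an independent or preoperative level is achieved", so a preoperative score must exist.

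**The concern.** In a linear model for a quantitative outcome, a covariate that predicts the outcome takes variation out of the residual and narrows the interval for the treatment effect. Eligibility spans a wide range of age and three ASA grades, and about 50 patients per arm are expected in the analysis. Age, ASA grade and starting mobility are plausible predictors of how fast a patient recovers, and the preoperative EMS score enters the definition of one of the five recovery criteria. The article gives power and precision as its reason for adjusting the secondary outcomes, but the main comparison has no patient-level adjustment in the model as stated.

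What is at stake is the width of the primary confidence interval and some reserve of power, not the validity of the comparison. Naming the covariates in advance also rules out choosing them after the data are seen.

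**Working it through.** **Inputs from the article (Sample size).** Target difference: "We are aiming for a reduction in time to functional recovery of 2 days". Spread: "given a within-arm SD of 2.73 with effect size" 0.73. Two-tailed α = 0.05, power 90%, withdrawal at most 10%, at least 10 centres, one extra patient per arm per additional centre.

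**Input assumed.** R² = 5%, 10% and 20%. The article gives no correlation between any baseline value and time to functional recovery.

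**1. The plan's own figures.**
- n per arm = 2 × (1.960 + 1.282)² × 2.73² / 2² = 39.2, so 40. A t-based calculation gives 41.
- Power at 40 per arm: 90.6% by the normal approximation, 89.9% by the non-central t.
- 40 / 0.9 = 44.4, so 45; plus 10 for centres = 55 per arm, 110 in total.

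Both 40 and 55 reproduce.

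**2. Analysed numbers.** 110 × 0.9 = 99, or 49.5 per arm; 49 per arm in whole patients. Ten centres with treatment × centre use 20 degrees of freedom, which leaves 98 − 20 = 78 (79 with 99 patients). Age and EMS take one each and ASA grade one or two, so adjustment costs three or four more.

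**3. Effect of adjustment.** Residual SD = 2.73 × √(1 − R²). Standard error = residual SD × √(2/n). Half-width = t × standard error. Power is from the non-central t. Arms are taken as balanced within centres.

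| Assumed R² | Residual SD | Power, 49 per arm | Half-width (days), 99 patients |
|---|---|---|---|
| none | 2.730 | 94.8% | 1.09 |
| 5% | 2.661 | 95.7% | 1.07 |
| 10% | 2.590 | 96.5% | 1.04 |
| 20% | 2.442 | 97.9% | 0.98 |

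First row: 1.99 × 2.73 × √(2/49.5) = 1.09. With 49 per arm it is 1.10, and the other three half-widths are unchanged to two decimals.

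**4. A deduction.** The table treats the arms as balanced on the covariates. In a randomised sample, chance imbalance multiplies the adjusted variance on average by about 1 + k/(residual degrees of freedom − 1), for k covariate terms:
- k = 3: 1 + 3/74 = 1.041. Variance relative to unadjusted is 0.95 × 1.041 = 0.99 at R² 5%, 0.94 at 10% and 0.83 at 20%.
- k = 4: 1 + 4/73 = 1.055. The ratios are 1.00, 0.95 and 0.84.

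The table is therefore an upper figure. At R² = 5% the average gain is close to nil; at 10% to 20% the variance falls by about 5% to 17%.

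**The case against.** The case against is substantial, and most of it stands.

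- **Power is not given away.** A reader might infer that the trial is underpowered without covariates. It is not: 90% is met under the plan's own inputs, and about 95% with 49 analysed per arm. The table's gain in half-width is 0.02 to 0.11 days, on an endpoint scored twice daily. One qualification is that the SD of 2.73 describes hospital stay, not functional recovery, in 31 patients at one centre, with and without ERAS. If the SD were 3.5 (an assumption), power with 99 patients would be 80.2% unadjusted, 84.1% at R² 10% and 88.0% at 20%, before the deduction above.
- **The article does not contradict itself.** It is tempting to set the secondary-outcome rule against the primary model. The covariate in that rule is the baseline value of the outcome itself, as for quality of life. Time to functional recovery has no such value, so there is no inconsistency.
- **The Background sentence does not bear on the primary endpoint.** "This delay is often linked to patient age, hospital logistics, and absence of social and/or homecare support" refers to the interval between functional recovery and discharge, in a study of colonic surgery. It supports age as a covariate for LOS. No section shows that age, ASA grade or EMS predicts time to functional recovery.
- **EMS may contribute little.** The mobility criterion is met at an independent or a preoperative level, so a low starting score may set an easier target. The direction and form of any association are unclear.
- **Chance imbalance is not bias.** Randomisation keeps the unadjusted estimate unbiased, and its interval already allows for imbalance.
- **Covariates may be in an analysis plan not shown.** The article does not say that other terms are excluded. But it does state the terms of the primary model and allows degrees of freedom for those alone, so the comment addresses a stated choice, not a missing detail.

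**Conclusion.** The point holds as a recommended improvement to a stated model, not as the correction of an error. The primary model names centre and treatment × centre and no patient-level covariate, while three reasonable candidates are available before surgery at almost no cost.

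The benefit is modest and conditional. For assumed R² of 5%, 10% and 20%, power rises from about 95% to at most about 96%, 96.5% and 98%, and the half-width falls from about 1.09 to no less than 1.07, 1.04 and 0.98 days. This rests on an R² that the article does not give, on the planned SD, on arms balanced within ten centres and on 10% withdrawal. If the covariates explain only about 5%, there is on average little or nothing to gain; at 10% to 20% the gain is real but small. Nothing here calls the stated sample size or the validity of the unadjusted comparison into question.

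**What to change.** Add one sentence to Univariate analysis: the primary model for time to functional recovery also includes age (continuous), ASA grade and preoperative EMS score as pre-specified covariates, with the result without these covariates reported as a sensitivity analysis. For LOS, pre-specify age and ASA grade.

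Two conditions apply:
- State when the preoperative EMS is taken. Patients are randomised at the outpatient clinic, and the article does not place the EMS before that. It should be scored before randomisation, or at least before surgery with the patient still blinded.
- Do not adjust for the operative part of P-POSSUM, which arises after randomisation.

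The cost is three or four of about 78 residual degrees of freedom. No new measurement and no change to the sample size is needed.

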#### Liver resection-specific composite endpoint

In this trial, we will also use a well-defined liver surgery-specific composite endpoint, as suggested by van den Broek *et al*. [38]. This endpoint is a parameter composed of a combination of procedure-specific complications, which is considered as a single, dichotomous outcome: operative mortality, intra-abdominal haemorrhage, ascites, bile leakage, intra-abdominal abscess, and post-resectional liver failure. These components, which are all specific to liver surgery and have substantial clinical relevance, reflect complications rated as Dindo grade 3–5. A composite score of 1 (failure) will reflect the occurrence of at least one of the above liver-specific complications, and a score of 0 (success) will be assigned if none of these occur.

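### The 75% power stated for all secondary outcomes does not carry over to the binary ones; total morbidity gets no effect estimate, and the rule for the liver-specific composite is unclear

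*Protocol article*

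**What the plan says.** All references are to the protocol article; no separate SAP is at hand.

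- **Primary & secondary endpoints** lists "total morbidity (both general and procedure related), composite endpoint of liver-surgery-specific morbidity, QOL, body image and cosmesis" among the secondary endpoints, so total morbidity and the composite are separate items. Readmissions and incisional hernia, also binary, are on the same list.
- **Liver resection-specific composite endpoint** defines a 0/1 variable, "which is considered as a single, dichotomous outcome: operative mortality, intra-abdominal haemorrhage, ascites, bile leakage, intra-abdominal abscess, and post-resectional liver failure". Its components "reflect complications rated as Dindo grade 3–5".
- **Sample size**: "For all secondary outcome measures, the power will be 75% after correction for multiple testing". The sentence sets two-tailed alpha at 0.01 and assumes the effect size used for the primary outcome, d = 0.73. It makes no exception for binary outcomes.
- **Descriptive statistics** says that morbidity will be graded by the published classification and "defined as a dichotomous composite endpoint".
- **Univariate analysis** sends all secondary outcomes measured at discharge to fixed-effect regression, "using linear regression for quantitative outcomes and logistic regression for binary outcomes", with the baseline measure as covariate and confidence intervals for all effects. The paragraph ends by saying that graded morbidity "will be presented as raw data only because the required sample size for intervention effects on morbidity is much larger" than the size calculated for this trial.

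**The concern.** Two statements about the same endpoints conflict. One section credits every secondary outcome with 75% power. Another says that the trial is far too small to assess intervention effects on morbidity, which is one of those outcomes. A reader of the power statement would expect the complication comparison to be informative, and it will not be.

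The analysis rule adds a second problem. Low power is a good reason not to test morbidity, but not a reason to withhold the difference and its interval. The interval is what shows how much harm or benefit the data leave open. Similar raw counts in the two arms can be taken as evidence of similar safety when the trial cannot exclude a sizeable difference.

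The composite falls between the two rules. Different analysts could give it a logistic-regression P-value or bare counts, and both could cite the article.

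**Working it through.** **Inputs from the article (Sample size).** SD 2.73, target difference 2 days, d = 2/2.73 = 0.73, 40 per arm before inflation, 55 per arm after it, and two-tailed alpha 0.01 for secondary outcomes. **Assumed:** event rates of 5%, 10% and 20%, because the article gives none for morbidity or the composite.

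**Step 1: the stated 75%.** For a continuous outcome, power = Φ(d·√(n/2) − z0.995). With n = 40 this is Φ(0.73 × √20 − 2.576) = Φ(3.265 − 2.576) = Φ(0.689) = 75.5%. The noncentral t version gives 73.2%. The figure is therefore reproduced, for a continuous outcome with 40 per arm.

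**Step 2: the same effect for a binary outcome.** The logistic conversion is OR = exp(d·π/√3) = exp(0.73 × 1.814) = exp(1.324) = 3.76.

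**Step 3: power at alpha 0.01 with 40 per arm.** The second risk p2 comes from dividing or multiplying the odds by 3.76. Power = Φ(|p1 − p2|/SE − 2.576), with SE = √[(p1(1 − p1) + p2(1 − p2))/40].

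| Change | Difference | SE | Power |
|---|---|---|---|
| 5% to 1.4% | 0.036 | 0.039 | Φ(−1.65) = 5% |
| 10% to 2.9% | 0.071 | 0.054 | Φ(−1.26) = 10% |
| 20% to 6.2% | 0.138 | 0.074 | Φ(−0.71) = 24% |
| 10% to 29.5% | 0.195 | 0.086 | Φ(−0.32) = 37% |

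If the null variance is pooled instead, the four powers are 5%, 10%, 22% and 34%. The choice of formula does not affect the conclusion. With 40 per arm and a 5% rate, only 2 events per arm are expected, so the first row is a rough approximation.

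**Step 4: is the reason for the raw-data rule sound?** For a halving from 10% to 5% with 75% power at alpha 0.01, n per arm = [2.576·√(2 × 0.075 × 0.925) + 0.674·√(0.10 × 0.90 + 0.05 × 0.95)]²/0.05² = (0.960 + 0.250)²/0.0025, about 586. From 5% and 20% the same formula gives about 1220 and 269. The article is right that the sample needed is much larger, and this is why its blanket 75% cannot cover morbidity.

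**Step 5: what an interval would show.** Illustrative counts with 55 per arm and Newcombe's method:
- 4 versus 4 events: the Wilson limits for 4/55 are 2.9% and 17.3%. The risk difference is 0, with limits ±√[(0.073 − 0.029)² + (0.173 − 0.073)²] = ±10.9 percentage points.
- 6 versus 3 events: the risk difference is +5.5 points (95% CI −5.6 to +16.9), and the odds ratio is 2.12 (0.50 to 8.96).

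Equal counts are thus compatible with a difference of about 11 points in either direction, which the counts alone do not show.

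**Step 6: which rule governs the composite?**
- For the raw-data rule: Descriptive statistics links graded morbidity to a dichotomous composite, and the composite's components are tied to grades of the same classification.
- For the logistic rule: the endpoint list and the endpoint subsections treat the two as separate outcomes, the raw-data sentence does not name the composite, and the composite is binary.

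The article does not decide between them.

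**The case against.** Several stronger readings are tempting, and the article does not support them.

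- **That the Univariate analysis section contradicts itself.** It states a general rule and then, in the same paragraph, a reasoned exception, which is ordinary drafting. The general rule also fits complications poorly, since they have no baseline measure to adjust for. For graded morbidity the analyst's instruction is clear. The conflict that remains is with the power sentence in Sample size.
- **That the composite certainly gets no effect estimate.** The raw-data sentence reaches it only through the loose wording in Descriptive statistics. On the other reading it keeps logistic regression and an interval. What the article shows is ambiguity.
- **That power and a model were specified for the composite.** Both come from blanket sentences about secondary outcomes.
- **That the 75% should be set against the power to detect a halving of risk.** The 75% is conditional on d = 0.73. A halving from 10% to 5% is an odds ratio of about 2.1 (0.111/0.053), a smaller effect. The fair comparison is the odds ratio of 3.76 used in Steps 2 and 3.
- **That the trial conceals harm.** The article says openly that it cannot address morbidity: the Discussion calls it infeasible as the trial's endpoint, and a data and safety monitoring board assesses safety. Readers could also compute an interval from published counts.

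It can also be said that the tabulation of descriptive safety data belongs in an SAP. That would dispose of a silence. Here, however, the article states a power figure and a raw-data-only rule, and both can be judged as written.

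**Conclusion.** The point holds in a limited form. The 75% power is correct for a continuous secondary outcome with d = 0.73 and 40 per arm, and wrong as a statement about all secondary outcomes. For an equivalent odds ratio of 3.76, power with 40 per arm is about 5% to 24% for a fall from 5% to 20%, and about 37% for a rise from 10% to 29%. These figures rest on assumed event rates, the logistic conversion of d and a normal approximation. Different rates would change them, and power rises with the event rate.

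Total morbidity is left without an effect estimate or interval. For the composite, the article supports only the statement that its rule is unclear. The primary analysis is not affected. What is affected is the accuracy of a stated power figure and the usefulness of the trial's complication comparison.

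**What to change.** 1. In Sample size, limit the 75% power sentence to continuous secondary outcomes. Add that it does not apply to the binary ones: total morbidity, the liver-specific composite, readmission and incisional hernia.
2. In Univariate analysis, state one rule for total morbidity and the composite: report the risk difference between the randomised arms with a 95% confidence interval by a small-sample method such as Newcombe's, as a descriptive result and without a significance test. Exempt both from the logistic-regression sentence.
3. In Descriptive statistics, separate graded total morbidity from the 0/1 composite so that the two are not read as one variable.

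The cost is a few sentences and two intervals, with no new data or patients. The drawbacks are a less favourable power statement and wide intervals, roughly ±11 points in the example of equal counts.
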